### Sample size and statistical methods

The sample size calculation of the study was based on China’s Ministry of Health data suggesting that at least 197 patients are required in each group for the final analysis to achieve a power of 80% to demonstrate a recurrence rate of 7%, rather than 16% resulting from *HuoXueSanFeng* acupuncture (data not shown, please see Additional file 1), at a two-sided significance level of 5%. Given a projected dropout rate of 15%, we aimed to recruit 480 patients for the study.

Statistical analysis will be conducted by a third party who is unaware of the treatment allocation. Data will be analyzed with SAS 9.1 and SPSS 19.0 software packages. Two-sided *P* < 0.05 represents statistical significance for all the analyses. Both intention-to-treat analysis (ITT) and per-protocol (PP) analysis will be performed. We will compare the result of ITT analysis with that of PP analysis to determine whether the results are consistent. For the ITT analysis, missing data will be handled by Last Observation Carry Forward rules, in brief, the finally observed data will be used for replacement of the missing primary variables.

Baseline demographic characteristics, including individual variables, such as age, sex, history of atrial fibrillation with or without current anti-coagulation medication, history of diabetes and smoking, and other baseline values, will be expressed with descriptive statistics for the two groups. For the primary outcome, recurrent stroke events, and secondary outcomes, the mortality rate and detailed causes (stroke or non-stroke), will be described as percentage (%), between-group difference will be analyzed using the chi-square test or Fisher’s exact test. For filling in the daily BP diary, it is required to measure BP four times each day at baseline before treatment, 2 weeks, 6 weeks, 12 weeks, 6 months, and 1 year after treatment. We will compare between-group or within-group values at the indicated time points. For highly effective use of the daily BP data, on one hand, we will collect all the values of the measurements at the same time in the day until each predesigned time point for comparison and, on the other hand, we will collate the four daily measurements to yield an average value in a day for later comparison at the time points mentioned above. Other secondary endpoints at different time points will also be compared. All the above different time-point assessments will be analyzed by repeated measures analysis of variance (ANOVA). Adverse events in each group will be documented as percentage (%) for safety assessments using the chi-square test or Fisher’s exact test.

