### Inclusion criteria

Patients will be further screened for eligibility if they fulfill all of the following inclusion criteria: (1) first-ever ischemic stroke that has been confirmed by cranial computed tomography (CT) or magnetic resonance imaging (MRI), with stroke duration over 2 weeks and less than 6 weeks; (2) BP below 160/100 mmHg on using one antihypertensive medication except the fixed-dose combinations, for at least 2 weeks; (3) aged 35 to 70 years; and (4) voluntary informed consent signed.

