### Outcome assessments

The assessors are blinded to grouping. The primary outcome will be all cases of recurrent stroke over a follow-up period of 9 months after receiving 12-week acupuncture treatments. Secondary endpoints, such as 24-h ambulatory BP, TCM syndrome score, Short Form 36-item Health Survey (SF-36) results, National Institute of Health Stroke Scale (NIHSS) and Barthel Index (BI) scale scores will be assessed at baseline, 6 weeks, and 12 weeks post initiating treatments; serum nitric oxide (NO), endothelin (ET), homocysteine (Hcy), soluble CD40 ligand (sCD40L), and copeptin levels and cardiac ultrasound, carotid artery ultrasound, transcranial Doppler, and lower extremity ultrasound results will be evaluated at baseline and 12 weeks after treatment. Other safety indicators including baseline general physical examination, blood, urine, and stool routine tests, coagulation function, D-dimer level, liver and kidney function, electrocardiograph as well as a chest X-ray will also be examined 12 weeks after randomization. At 6 months after randomization, blood, urine, and stool routine tests, coagulation function, D-dimer level, liver and kidney function, electrocardiograph, NO, ET, Hcy, sCD40L, and copeptin tests will be re-checked, with some hope of improving patients’ adherence to treatment. All-cause mortality will also be evaluated during the follow-up period. The Essen Stroke Risk Score (ESRS) will be additionally assessed at baseline and 1 year post randomization.

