### Follow-up

After finishing the acupuncture treatments, patients will be followed up monthly via telephone for 1 year post randomization. Stroke recurrence, all-cause deaths and BP control will be investigated and recorded in the CRFs. The patients will be required to use the BP diaries to record their BP four times daily. If the BP is ≤ 160 mmHg systolic and/or ≤ 100 mmHg diastolic for 1 month, the patient will be advised to take antihypertensive medications, which will be documented in the CRF.

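### Carrying the last observation forward on the yes/no primary outcome counts each patient lost without a recorded stroke as stroke-free to the end of follow-up

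*Protocol article*

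**What the plan says.** Under Sample size and statistical methods, the protocol article states: "For the ITT analysis, missing data will be handled by Last Observation Carry Forward rules". It then names the variable concerned: "the finally observed data will be used for replacement of the missing primary variables". Outcome assessments gives a single primary outcome: "The primary outcome will be all cases of recurrent stroke over a follow-up period of 9 months after receiving 12-week acupuncture treatments". This is reported as a percentage, and the "between-group difference will be analyzed using the chi-square test or Fisher’s exact test". No censoring is described.

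Inclusion criteria admits only patients whose index ischaemic stroke is their first. Under Follow-up, "patients will be followed up monthly via telephone for 1 year post randomization" and "Stroke recurrence, all-cause deaths and BP control will be investigated and recorded in the CRFs". Table 1 schedules recurrence at week 48 only. The article projects 15% dropout and, in its Discussion, accepts that compliance over the 9 months may be difficult. The only cross-check it names is a comparison of the intention-to-treat and per-protocol results.

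**The concern.** Carrying a value forward presumes a measurement that could plausibly have stayed where it was. Recurrence is an event that accrues over time and starts at no for everyone. For a patient who disappears without a recorded stroke, the last value can only be no, so the rule turns partial or absent follow-up into complete, event-free follow-up. If Table 1 is read literally and recurrence is assessed only at week 48, the only earlier value is the event-free entry state, and the score is the same.

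Two things are at stake. The recurrence risks reported for each arm will be too low. And if the arms lose different proportions of patients, the chi-square test compares risks diluted by different amounts, so part of any observed difference would reflect retention. The rule is stated for the only primary endpoint, so a more detailed analysis plan would have to overturn it and could not merely fill a gap.

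**Working it through.** **The plan's own figure first.** Inputs from the sample-size paragraph: 16% versus 7%, two-sided 5%, 80% power. With the pooled-variance formula and mean risk 0.115:

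n = [1.960 × √(2 × 0.115 × 0.885) + 0.842 × √(0.16 × 0.84 + 0.07 × 0.93)]² / 0.09² ≈ 1.588 / 0.0081 ≈ 196.1, rounded up to 197 per group.

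This matches the article. Dropout: 197 / 0.85 = 231.8, so 232 per group and 464 in total. The 480 planned covers this and tolerates loss up to 1 − 197/240 = 17.9%. The sample size is not in error.

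**Effect of the rule.** Let p be an arm's true risk, d the proportion lost with no recorded event and no final outcome, and f the share of a lost patient's stroke risk that falls after last contact. Then

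recorded risk = p × (1 − d × f).

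f = 1 means that all loss precedes the outcome window (the upper bound). f = 0.5 approximates loss spread evenly over it. Assumptions not given in the article: the values of f, any unequal split of d, and equal stroke risk in lost and retained patients.

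**Equal loss at the planned 15%.**

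- f = 1: control 0.16 × 0.85 = 13.6%; experimental 0.07 × 0.85 = 5.95%; difference 7.65 points.
- f = 0.5: control 0.16 × 0.925 = 14.8%; experimental 0.07 × 0.925 = 6.475%; difference 8.3 points.
- True difference: 9.0 points. The risk ratio is 7/16 = 5.95/13.6 = 0.4375 throughout.
- Power with 240 per arm by normal approximation: 80.8% (f = 1) and 84.3% (f = 0.5). For comparison, 204 completers per arm (240 × 0.85) give 81.5%.

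**Unequal loss, no true effect** (16% in both arms, 240 per arm). With recorded risks a (control) and b (experimental), the rejection probability uses the pooled standard error for the critical value and the unpooled one for the spread. For 10% versus 20% loss and f = 1: a = 0.144, b = 0.128, pooled SE = 0.0313, unpooled SE = 0.0313. The upper limit is (1.960 × 0.0313 − 0.016) / 0.0313 ≈ 1.449, giving 7.4%. The lower tail adds 0.7%, for a total of 8.0%.

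| Loss, control / experimental | f | Recorded risks, control / experimental | Risk ratio | Two-sided rejection |
|---|---|---|---|---|
| 10% / 20% | 1 | 14.4% / 12.8% | 0.89 | 8.0% |
| 10% / 20% | 0.5 | 15.2% / 14.4% | 0.95 | 5.7% |
| 5% / 25% | 1 | 15.2% / 12.0% | 0.79 | 17.5% |
| 5% / 25% | 0.5 | 15.6% / 14.0% | 0.90 | 7.8% |

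**The reverse split.** With no true effect, exchanging the two loss rates gives the same rejection rates, now mostly favouring control. With the planned effect (16% versus 7%) and 20% control / 10% experimental loss, the recorded risk ratio is 0.49 with power 68% (f = 1), or 0.46 with power 79% (f = 0.5).

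**The case against.** The strongest case for leaving the rule alone is that, at the article's own 15% in both arms, it causes neither a false positive nor a material loss of power. That stands. So do these points:

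- A reader might infer that every dropout is scored stroke-free. The article does not support that. Informed consent says withdrawn patients' available data are kept, so a stroke recorded before withdrawal still counts. Leaving treatment is also not the same as a missing outcome: Data management and quality control allows information from medical records and from a relative or proxy. Treating the full 15% as unknown is an upper bound.
- A reader might infer that the test is tilted towards acupuncture, since only the experimental arm has the extra needling and the provision for stopping antihypertensives. Nothing in the article projects unequal loss. Both arms are needled at the same frequency, and the shared acupuncture is offered free partly to aid adherence. Controls could equally be lost more often.
- The 17.5% figure needs a fivefold difference in loss with every loss before the window opens, whereas recruitment is of inpatients for the first 6 weeks and the Discussion places the compliance problem in the later follow-up.

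The planned per-protocol comparison is a weaker defence. The article does not define that set. If it excludes lost patients, and loss is unrelated to stroke risk, it would recover the true risks and might expose a discrepancy. But it simply assumes that the lost resemble the retained. It does not test what happens if they do not.

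**Conclusion.** The point holds in this form. The stated rule counts patients lost without a recorded event and without a final outcome as stroke-free for the whole window. At the planned equal loss, the recorded risk difference falls from 9.0 points to between 7.65 and 8.3, with the risk ratio and planned power intact. Distortion of the test is conditional: it needs unequal loss, and it favours the arm with more loss when lost and retained patients have similar stroke risk. Under that assumption the rejection rate is 5.7–8.0% for a 10-point imbalance and 7.8–17.5% for an extreme 20-point one, against a nominal 5%. If lost patients carry higher stroke risk than retained ones, the absolute risks are understated further. The article gives no ground for claiming that the bias will run towards acupuncture, or that the 17.5% figure is likely. Severity: should be fixed.

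**What to change.** Delete last observation carried forward for the primary outcome and keep the stated 9-month post-treatment window. Estimate each arm's recurrence risk at the end of that window with patients censored at last contact, using Kaplan–Meier or, with death without stroke as a competing event, cumulative incidence. Report the risk difference with its confidence interval. Starting the clock at randomisation is not part of this change, because it would alter the stated outcome.

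Censoring also assumes non-informative loss, so add a tipping-point or multiple-imputation sensitivity analysis that gives lost patients higher stroke risks, varied by arm. Before either analysis, use medical records and proxies to reduce the number of missing outcomes.

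The cost is analysis wording and a little more analysis work. The case report form must also hold the month of each event and the date of last contact. The article does not say that dates are recorded, but the monthly calls can supply both at least to the month. No extra patients or visits are needed.

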### Randomization and allocation concealment

All the eligible participants will be randomized into the experimental group or the control group, in a 1:1 ratio, using minimization, a dynamic random allocation technique by the MINIM program installed in each separate center. The baseline prognostic factors related to stroke recurrence, including age, categorized as 35–50, 51–65, and 66–70 years), gender, smoking status, diabetic status and atrial fibrillation, classified as “no” or “yes with/without anti-coagulation,” will be balanced between groups according to the minimization procedures. The computer-generated randomization grouping code will be offered after the recruitment of the eligible patients so that allocation concealment should be ensured.

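### The stated analyses make little use of the minimisation factors, centre and baseline values: a small loss of power for recurrence, a larger one for the continuous secondary outcomes

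*Protocol article*

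**What the plan says.** **Allocation.** Under Randomization and allocation concealment, patients are assigned "using minimization, a dynamic random allocation technique by the MINIM program installed in each separate center". The factors are introduced as "The baseline prognostic factors related to stroke recurrence, including age" (three classes), followed by "gender, smoking status, diabetic status and atrial fibrillation", and they "will be balanced between groups according to the minimization procedures". There are five centres. Because the program runs separately in each, allocation is in effect stratified by centre.

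**Recurrence and mortality.** Under Sample size and statistical methods, the minimisation factors appear again, but only for descriptive summary by group. For recurrence and mortality, "between-group difference will be analyzed using the chi-square test" or Fisher's exact test. No adjusted or centre-stratified analysis is named.

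**Repeated outcomes.** The same section states: "All the above different time-point assessments will be analyzed by repeated measures analysis of variance (ANOVA". For diary blood pressure the time points are baseline, 2, 6 and 12 weeks, 6 months and 1 year. Ambulatory blood pressure, the TCM score, SF-36, NIHSS and Barthel Index are measured at baseline, 6 and 12 weeks (Table 1; Outcome assessments). Comparisons may be between or within groups. No covariate is named, and nothing says which ANOVA effect is the treatment test.

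**The concern.** If the factors are prognostic, as the article says, balancing them reduces the true variability of the difference between arms. An unadjusted test does not credit that reduction. Its standard error is somewhat too large, so it is conservative and gives up some power.

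For the continuous outcomes, baseline is treated as a response and not as a covariate. A group main effect then averages in a time point at which no treatment effect can exist. A group-by-time test compares changes from baseline, which is generally less precise than adjusting for baseline. With no contrast named, the reader cannot tell which of the two will be reported as the treatment effect.

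Within-group comparisons add a difficulty of interpretation. Inclusion and exclusion criteria select patients whose blood pressure is uncontrolled but below 160/100 mmHg. Some fall from regression to the mean is therefore to be expected in both arms, and a within-group test cannot separate it from a treatment effect.

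**Working it through.** **1. The plan's own figure.** Inputs from the sample-size section: 16% against 7%, two-sided 5%, power 80%. With pooled variance and no continuity correction:

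- mean rate = (0.16 + 0.07)/2 = 0.115
- 1.960 × √(2 × 0.115 × 0.885) = 0.884
- 0.842 × √(0.16 × 0.84 + 0.07 × 0.93) = 0.376
- n = (0.884 + 0.376)² / 0.09² = 196.1, so **197 per group**, as stated.

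Power at 197 is 80.2%. After 15% dropout, 480 × 0.85 / 2 = 204 per group, with power 81.5%. The sample size fits the unadjusted chi-square test.

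**2. Recurrence: chi-square against an adjusted test.** The article gives no covariate–outcome strengths, so these are assumed.

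- Design: 394 patients, five centres, minimisation within centre on the five factors (biased coin 0.8, assumed), 2,000 trials per setting.
- Strengths: the odds ratio (OR) below applies in full to each age class, diabetes and atrial fibrillation. Smoking has 0.5 and sex 0.3 of its logarithm. Centre effects run from minus to plus one times its logarithm.
- Adjusted test: logistic regression on the factors and centre.

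| Assumed OR | Type I error, chi-square / adjusted | Power, chi-square / adjusted |
|---|---|---|
| 1.0 | 5.3% / 5.5% | 82.2% / 82.2% |
| 1.5 | 5.0% / 5.5% | 81.6% / 82.3% |
| 2.0 | 4.9% / 5.7% | 82.1% / 84.0% |
| 3.0 | 2.9% / 4.5% | 83.1% / 87.5% |

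The Monte Carlo standard error is about 0.5 points for type I error and 0.9 points for power. A simpler simulation (408 patients, four binary factors, exactly balanced strata, 4,000 trials) agrees:

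- OR 1.5: power 80.5% against 80.8%.
- OR 2.5: power 77.9% against 80.4%, type I error 4.2% against 5.2%.

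**3. How large a model the events allow.** Expected events = 0.16 × 197 + 0.07 × 197 = 31.5 + 13.8 = 45.3. Treatment (1), age (2), sex, smoking, diabetes and atrial fibrillation (1 each) and centre (4) make 11 parameters, so 45.3 / 11 ≈ 4 events per parameter.

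**4. Continuous outcomes: variance.** Let r be the correlation between baseline and follow-up (assumed). Relative to comparing follow-up values, change scores have variance 2(1 − r) and baseline adjustment has 1 − r². The ratio of baseline adjustment to change is (1 + r)/2.

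| r | Adjusted / follow-up | Adjusted / change |
|---|---|---|
| 0.5 | 0.75 (25% less) | 0.75 (25% less) |
| 0.6 | 0.64 (36% less) | 0.80 (20% less) |
| 0.7 | 0.51 (49% less) | 0.85 (15% less) |

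**5. Continuous outcomes: dilution.** With k levels including baseline and a constant effect afterwards, the group main effect is (k − 1)/k of the true effect. With k = 3 (the scales and ambulatory blood pressure) one third is lost. With k = 6 (diary blood pressure) one sixth is lost.

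**6. What this does to power.** Assume baseline plus two visits, compound symmetry, an equal effect at both visits, and 90% power for the baseline-adjusted average. The group main effect then has power 46% at r = 0.5 and 39% at r = 0.6. The two-degree-of-freedom group-by-time test has 66% and 70%.

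**The case against.** The strongest reply is that the planned chi-square is valid, matches the sample-size calculation and is adequately powered for its stated assumptions. That stands. A reader might infer from the mismatch with minimisation that false positives are inflated or that the sample size is wrong. Neither follows: the chi-square showed no inflation in any setting, and at OR 3.0 it was conservative. At OR 1.5 the difference in power is within simulation error.

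A reader might also infer that baseline is ignored in the repeated outcomes. It is not. Baseline is a time level, so a group-by-time test compares changes. The one-third dilution arises only if the group main effect is the treatment test, which the article does not say, and for diary blood pressure it would be one sixth.

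Nor do the documents support saying that ANOVA will drop every patient with a missed visit. The intention-to-treat analysis has a last-observation-carried-forward rule. Its explanation mentions primary variables, so its reach to secondary outcomes is unclear, but dropping is not settled.

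The article attaches no efficacy claim to within-group results, so the concern there is how they might be read.

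Finally, covariates and contrasts are often left to an analysis plan, which is not shown. That carries limited weight here, because the article does name the test for recurrence and the method for repeated outcomes.

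**Conclusion.** The point holds as one of efficiency and clarity, not validity. For recurrence, the unadjusted test costs under 1 point of power at OR 1.5, about 2 points at 2.0 and about 4 points at 3.0. These strengths are assumptions, and the last goes with large differences between centres. Part of the gain at 2.0 may reflect the adjusted test running slightly above 5% in the simulation.

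The continuous secondary outcomes are the stronger part. At an assumed r of 0.5 to 0.6, adjustment cuts variance by 20–25% against change and 25–36% against follow-up values. The gain over change shrinks as r rises. Leaving the treatment contrast unnamed is a defect whatever r turns out to be.

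**What to change.** 1. **Continuous secondary outcomes.** Use a mixed model on the post-baseline visits with baseline value, treatment, visit, treatment-by-visit and centre. Name the between-arm contrast that is the treatment test. Label within-group comparisons as descriptive only.
2. **Recurrence.** Prespecify a sparse adjusted analysis, for example a centre-stratified test, or penalised logistic regression on the minimisation factors reported as a standardised risk difference. The risk difference keeps the result on the scale of the powered 7% against 16% comparison, which a hazard or odds ratio alone would not. Keep the chi-square as supportive.
3. **Atrial fibrillation.** It is a minimisation factor, while the exclusion criteria list arrhythmia. The two sections must be reconciled before it enters any model.

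**Cost.** No extra patients are needed, and the factors, centre and baseline values are already recorded. There is slightly more analysis work than a change of wording, and the recurrence model must stay small because only about 45 events are expected.

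### One of the two diary BP summaries has an end date but no start; read literally, its 6-month and 1-year values include the 12 treatment weeks

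*Protocol article*

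**What the plan says.** All of this is in the protocol article. The section on sample size and statistical methods sets the diary time points "at baseline before treatment, 2 weeks, 6 weeks, 12 weeks, 6 months, and 1 year after treatment" and states the aim: "We will compare between-group or within-group values at the indicated time points". It then gives two ways of using the diary:

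- by clock time: "we will collect all the values of the measurements at the same time in the day until each predesigned time point for comparison";
- by day: "we will collate the four daily measurements to yield an average value in a day for later comparison at the time points mentioned above".

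Both go into repeated measures ANOVA. No start date or window is given for the first summary.

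The diary runs throughout the study. Table 1 has it filled in every day, and the Follow-up section says "The patients will be required to use the BP diaries to record their BP four times daily". Acupuncture lasts 12 weeks, and the primary outcome is counted "over a follow-up period of 9 months after receiving 12-week acupuncture treatments". Table 1 puts the late visits at weeks 24 and 48, and schedules 24-h ambulatory BP only up to week 12.

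**The concern.** A value meant to describe BP at 6 months or 1 year should contain readings from around that time. The clock-time rule, taken as written, collects everything recorded so far. The week-24 value would then contain all of weeks 1-12, and the week-48 value would contain those weeks again. The sets are nested, and repeated measures ANOVA would treat them as separate occasions.

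This matters because ambulatory monitoring stops at week 12. BP after treatment is known only from the diary and the follow-up BP entries at weeks 24 and 48. A reader who asks whether BP control outlasts the needling will look at these late comparisons. A running pool carries the on-treatment difference forward into them, and can equally cover up a deterioration once treatment ends.

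**Working it through.** **The plan's own figure.** The protocol gives no effect size, SD or power for diary BP. Its only computable figure is for stroke recurrence, 16% against 7%. With pooled variance and no continuity correction:

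n = [1.96·√(2·0.115·0.885) + 0.8416·√(0.16·0.84 + 0.07·0.93)]² / 0.09² = 196.06, so 197 per group.

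This matches the protocol, and the diary rule does not affect it. The number available for the diary is 480 × 0.85 = 408, or 204 per arm.

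**Inputs.** From the protocol: 12 treatment weeks, late visits at weeks 24 and 48, daily diary, 15% dropout, two-sided 5%. Assumed: an on-treatment difference d of 3, 5 or 8 mmHg in weeks 1-12 and exactly 0 afterwards; a between-patient SD of the pooled value of 10 to 15 mmHg; equal numbers of readings per week.

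**Step 1, share of treatment-period readings in the pool = 12/T.**

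- Week 24: 12/24 = 50%. Week 48: 12/48 = 25%.
- Counting 26 and 52 calendar weeks: 46% and 23%.
- Counting from the end of treatment (weeks 38 and 64): 32% and 19%. Week 64 lies beyond the one-year follow-up, so this reading fits the schedule poorly.

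**Step 2, apparent late difference = d × 12/T.** For d = 5 it is 2.5 mmHg at week 24 and 1.25 mmHg at week 48, when the truth is 0.

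**Step 3, chance of P<0.05.** SE = SD × √(2/204), which is 0.99 for SD 10 and 1.485 for SD 15. The chance is Φ(apparent difference/SE − 1.96). For d = 5, SD 10, week 24: 2.5/0.99 = 2.525 and Φ(0.565) = 71%.

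| d (mmHg) | Week 24, SD 10 | Week 24, SD 15 | Week 48, SD 10 | Week 48, SD 15 |
|---|---|---|---|---|
| 3 | 33% | 17% | 12% | 7% |
| 5 | 71% | 39% | 24% | 13% |
| 8 | 98% | 77% | 52% | 27% |

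The formula counts only rejections in the direction of the carried-over difference. The opposite tail adds at most 0.7 percentage points (7.3% becomes 8.0% in the smallest cell).

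**Step 4, check by simulation.** With weekly means, between-patient SD 9, within-patient SD 6, d = 5 and 2,000 runs, the pool was significant in 77% of runs at week 24 and 28% at week 48. Using only the last week before the visit, or only readings since the previous late visit or the end of treatment, gave 4-6% for every d tried (0, 3, 5, 8).

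**Step 5, the opposite error.** Suppose BP is 5 mmHg lower in the experimental arm during treatment and 5 mmHg higher afterwards. The pooled difference at week 24 is (−5 × 12 + 5 × 12)/24 = 0. At week 48 it is (−5 × 12 + 5 × 36)/48 = 2.5 mmHg, half the true 5.

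**The case against.** The strongest reply is that the sentence speaks of collecting readings, not of a cumulative mean, and gives no start. It could mean everything since the previous time point. The 6-month set would then begin after week 12 and the late bias would vanish. The sentence before it, which promises values at the time points, favours such a reading. This stands as a possibility, but the protocol does not say it. The plain sense of taking all values until a date is everything up to that date. This is also more than a detail left to an analysis plan, because an aggregation rule is stated and it conflicts with the stated aim.

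Three further points stand in full:

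- Only the clock-time summary is affected. A reader might infer that every 6-month and 1-year diary comparison is contaminated. The text does not support that: the daily average is tied to the time points and is not described as cumulative, and Table 1 has a separate follow-up BP row at weeks 24 and 48.
- Diary BP is not the primary outcome, and the secondary endpoints listed in the Abstract and under Outcome assessments name ambulatory BP rather than the diary.
- The effect and SD are assumptions. The medication rules, which differ between arms, could keep the on-treatment difference small, so the lower end of the range deserves as much weight as the upper.

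It might also be argued that having two summaries is itself a fault. That is weak: clock-time values and a daily mean answer different questions and can both be kept.

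**Conclusion.** The point holds for one of the two diary summaries. As written, its late values would be half (week 24) and a quarter (week 48) treatment-period readings, contrary to the stated aim. If a difference existed only on treatment, a false lasting effect would be declared in about 17-98% of trials at week 24 and 7-52% at week 48, under an assumed 3 to 8 mmHg, SD 10 to 15 mmHg and 204 per arm. The problem is largest at 6 months and modest at 1 year when the effect is small.

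These figures are conditional on the cumulative reading and on a difference that stops at week 12. They do not show that the trial will report a false effect, and they say nothing against the stroke recurrence analysis or the sample size. The rule should be corrected before the diary data are analysed, but it does not threaten the trial's main conclusion.

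**What to change.** For both summaries, replace the open-ended collection by one fixed, non-overlapping window per time point, for example the 7 days ending at it, and state that the 6-month and 1-year windows lie wholly after week 12. Count the time points from randomisation, in line with Table 1. Define the baseline window separately, as readings before the first session, because the diary is handed out only after randomisation. If a cumulative mean is still wanted, report it under its own name, as average BP since baseline, and not as BP at a visit.

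The cost is about one sentence in the protocol or analysis plan and a programming change, with no new data and no change in patient care. The downside is fewer readings per value. A 7-day window still holds up to 7 × 4 × 3 = 84 readings for the daily mean and 7 × 3 = 21 for each clock time.
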